**Fig. 1 Fig1:**
[figure not shown]
Overview of the study design and course of the spatial intervention study. T0 is the final appointment of the standard diagnostic investigation at the memory clinic. T1 & T2 are additional appointments for research interviews

**Table 1 Tab1:** Endpoints, potential predictors and measuring instruments

Measured quantity	Instrument and description	Time of assessment
Ability to ‘understand’, ‘appreciate’, ‘reason’ and ‘express a choice’ as preconditions of capacity to consent	CAT-AD: adjusted version of the DCAT-PAD/MacCAT-T [20, 21] for PwAD	T1 & T2
	Semi-structured interview	
Subjective task complexity	Subscale ‘post task: subjective task complexity’ [28]	T1 & T2
	4-item-subscale	
Decisional conflicts	Subscale ‘uncertainty’ of the German version of the ‘Decisional Conflict Scale’ [29]	T1 & T2
	3-item-subscale	
Anxiety in the decision-making situation	Single item described by LeBlanc et al. [30]	T1 & T2
Age, gender		T0
Education	Single item based on German education system	T0
Severity of dementia	Mini-Mental Status Examination [31]	T0
	Screening for cognitive abilities to detect cognitive impairment or dementia	
Severity of possible depression	Geriatric Depression Scale [32]	T0
	Screening for depression in the elderly	
Perceived sense of belonging to home	Selection of items from Meaning of Home Questionnaire [26, 27]	T0
	Adjusted for people with dementia & validated during the project	
	Guided interview	
Need of autonomy for medical decisions	Single item described by Strull et al. [33]	T0
Health literacy	Single item described by Morris et al. [34]	T0

As in our previous studies, the presentation of information will be standardised for both the intervention and the control settings in order to ensure as much consistency as possible in everything apart from the ‘place’. Consequently, all support strategies that have proven to be effective in our own and international studies (e.g., elaborated plain language, key word list, time of day: 8–15 o’clock, person-centred attitude), will be used in both places (as recommended in the current AWMF-S2k-guideline “Einwilligung von Menschen mit Demenz in medizinische Maßnahmen”; for a summary of available evidence on SDM for PwAD, see [7, 19]).

#### Adherence, retention, and withdrawal

In order to avoid selective drop-out due to the cognitive impairments of the participants, we have different strategies to ensure that they meet their appointments. When they agree to participate in the study, they receive a reminder note with the dates and location. Furthermore, we will call the participants and, if necessary, their relatives two days in advance to ensure that they do not forget their appointment. In case of a missed appointment, we will offer to make up for it on a later date. If a person rejects participating in the study or decides to end it early, we try to record the reasons for their rejection or cancellation.

### Outcomes

#### Primary endpoint

The primary endpoint in this study will be an assessment of capacity to consent to create an advance directive both at home and at the clinic using the Competence Assessment Tool—Advance Directive (CAT-AD). To create the CAT-AD, we adapted both the MacCAT-T [20] and the DCAT-PAD for advance directives in PwAD [21]. The MacCAT-T is a well-known international instrument for the standardised assessment of the capacity to consent to treatment options [22] and the DCAT-PAD is a version of the MacCAT-T that has been adapted for psychiatric advance directives. Both tools test participants’ ability to ‘understand’, ‘appreciate’, ‘reason’ and ‘express a choice’. As we expect the intervention to particularly support patients’ reasoning capacities, the corresponding subscore will be the primary endpoint of the study. The other subscores and the total score will be secondary endpoints. In view of our target population, we also reduced the complexity of the scale ‘*Understanding Risks and Benefits of Advance Directives’*. To meet German legal standards for informed consent, we added a further item to the scales *‘Appreciation’* and *‘Expressing a Choice’*. To compensate for the dominance of verbal recall shown in previous studies [23, 24], the information is presented to the participants in the form of bullet points [25].

#### Secondary endpoints and suspected moderators, mediators, and confounders

Besides the CAT-AD scores mentioned above, we will assess several secondary endpoints, as well as suspected moderators, mediators and confounders. Table 1 provides an overview of all endpoints and covariates, along with the corresponding measuring instruments. Further secondary outcomes are subjective task complexity, decisional conflicts and anxiety in the decision-making situation. Suspected moderators, mediators and confounders are severity of dementia and – if present – depression, the perceived sense of belonging to home, the need for autonomy in medical decision-making, health literacy, and such sociodemographic variables as age, gender, and education. The listed instruments were adjusted for the present study and our sample as appropriate. To assess the perceived sense of belonging at home, the ‘Meaning of Home Questionnaire’ [26, 27] will be revised and validated for PwAD as part of the DECIDE project. For the spatial intervention study, we will select the items that are most suitable for measuring the extent of perceived belonging based on theoretical and statistical considerations.

### Statistical methods

#### Analysis population

Since our intervention consists in making a decision at two different places in a certain order, the only possible reason why the intervention might not conform to the study protocol is – apart from missing data issues – that the sequence of the places is swapped. If this occurs, it will be due to an organisational error, i. e. completely at random. This means the patient can be analysed with the sequence group that corresponds to his or her actual sequence without generating any bias. Apart from this, as the appointments for the interviews involve two persons (study nurse and physician) checking the correct sequence independently, we consider such an error highly unlikely. Hence, the analysis population will be the “as treated” population.

#### Statistical analysis

A linear mixed model with place, period, and interaction of place and period as fixed effects and patient as a random effect will be used to analyse the primary endpoint. We will check for carryover by testing the interaction between place and period. If there is no significant interaction effect, differential carryover can be neglected. Otherwise, statistical analysis will be stratified by period, whereby the main analysis will be restricted to the first period, and data from the second period will be used for sensitivity analysis.

An exploratory investigation of the impact of the place the decision is made on subjective task complexity, decisional conflicts and anxiety will be based on a model that is analogous to the main analysis.

Furthermore, both linear mixed models will be extended to include an exploratory analysis of potentially confounding, moderating, and mediating variables.

The relationship between the place the decision is made, and the other secondary endpoints will be explored by conducting two-sample comparisons between the sequence groups in a two-step procedure based on Wilcoxon-Mann–Whitney tests, consisting of a pretest for differential carryover and a main test for the location effect. This is essentially equivalent to the mixed model approach but assumes no particular probability distributions and does not permit inclusion of covariates. If the pretest is significant, the main test will only be performed on data from the first period.

The features of the patient sample will be summarised descriptively. Absolute and relative frequencies will be used for categorical variables, and mean, standard deviation, minimum, maximum, and quartiles for metric variables.

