### Study design

We will use a randomised AB/BA crossover design to study the effect of the spatial intervention ‘decision-making place: home vs. memory clinic’ on capacity to consent to an advance directive. Each participant will undergo one session at the memory clinic and one session at their home. The decision where the first session will be conducted will be made randomly for each PwAD, and stratified by site. The crossover design will further permit us to examine the presence of substantial period and carryover effects.

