### Procedure

#### Data collection

The procedure of the spatial intervention study is presented in Fig. 1*.* Patients fulfilling the inclusion criteria will be asked whether they wish to participate at their final appointment at the memory clinic (T0). If they agree, the physician will assess suspected moderators, mediators and confounders including demographic variables, severity of dementia and depression, perceived sense of belonging to home, need for autonomy in medical decisions and health literacy (see Table 1). Afterwards, two further appointments will be made. Patients will be assigned to one of the two groups by using site specific randomisation lists with two levels (i.e., the order of visits) and a final block size of 4. These lists were created using R and the R package blockrand [17, 18]. At the beginning of each session (T1 & T2), the research physician will assess the capacity to consent of the individual to complete an advance directive, as well as subjective task complexity, decisional conflicts, and anxiety in the decision-making situation (see Table 1). As the decision-making situation should be as realistic as possible and also be of benefit to the participants, they will all have the chance to take part in ACP following the assessment. They can decide whether to create an advance directive with the help of the study physician, or whether to gather information on a possible care directive or lasting power of attorney. It is also possible to decide against ACP. The ACP process will be divided between the two sessions to avoid overload.

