#### Calculation of sample size

From a recent trial evaluating SDM strategies for patients with dementia (EmMa project) [9], the MacCAT-T subscale scores of the 30 patients with Alzheimer’s disease (14 in the intervention, 16 in the control group) were used to define the relevant standardised location effect for the sample size calculation. While the SDM strategies in EmMa project only increased scores on the “understanding” subscale of the MacCAT-T, we expect that in our trial, the support of the familiar environment of the patient’s home will rather influence the “reasoning” subscale. Thus, we anticipate that as a result of the DECIDE intervention, the change in the reasoning score will be similar to the standardised effect of 0.582 found for understanding in EmMa project.

Due to memory limitations in the study population, we do not expect any substantial carryover effect. The relevant quantity for the sample size calculation will therefore be the location contrast estimated from both periods. However, although unlikely to be detected in a cross-over design powered for the main effect of the place the decision is made, slight differential carryover will still bias the effect. Hence, the sample size should allow us to compensate for power loss due to undetected differential carryover of up to 20% of the spatial intervention effect.

Use of a cross-over design further means that only intra-individual variance must be taken into account. The stronger the correlation between a patient’s two observations, the smaller the intra-individual variance and the smaller the necessary sample size. Although we expect some positive correlation, we will assume uncorrelated observations to be on the safe side.

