Based on these assumptions, and with a two-sided significance level of α = 5%, the power.t.test () function of the R stats package (version 4.0.2) results in a total sample size of 80 patients, 160 observations, for a power of 90%. If recruitment difficulties arise, 80% power will still be achieved with 60 patients and 120 observations. If – as is to be expected – a positive correlation exists between the same patient’s measurements, even fewer patients will suffice to reach 80% power. For example, assuming a within-patient correlation of 0.2, the inclusion of 48 patients and 96 measurements will mean the power is still 80%. If a significant proportion of patients can only be studied once, the analysis could be restricted to the first observations. However, if 80 first measurements are available, the power for detecting the location effect will be reduced to 58%. In this case, we would try to include a further 16 patients and thus achieve 80% power.

Since a two-step evaluation procedure based on a linear mixed model will be used to analyse the primary endpoint, we verified the sample size in a simulation of the procedure with 10,000 analysis runs per scenario. Based on the relevant standardised effect (see above) and the variance in the ‘reasoning’ scores observed in EmMa project [9], we considered four scenarios covering a range of realistic outcomes. They are presented in Fig. 2. The simulation confirms the sample sizes obtained from the t-test formula.

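### Sequence is randomised within site, but the listed primary model and the rank tests omit site; the complete-pair place contrast is unaffected, while the between-patient steps become conservative and lose some power.

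*Protocol article*

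**What the plan says.** Under Study design, the choice of first location is "made randomly for each PwAD, and stratified by site". Under Data collection, allocation uses "site specific randomisation lists with two levels" (the two visit orders) and a final block size of 4. The Participants section plans 40 patients at each of two memory clinics. The section on principal and lead investigators makes the study physicians and neuropsychologists of each centre responsible for data collection, and Limitations states that the physicians cannot be blinded.

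Under Statistical analysis, the primary endpoint is analysed with "A linear mixed model with place, period, and interaction of place and period as fixed effects and patient as a random effect". The place-by-period interaction is tested as a check for carryover. If it is significant, the main analysis uses the first period only. For other secondary endpoints a two-step Wilcoxon-Mann-Whitney procedure compares the sequence groups: a carryover pretest, then the location test, again restricted to the first period if the pretest is significant. The article notes that this procedure takes no covariates. The mixed models are to be extended with potential confounders, moderators and mediators, but site is not in that list, in the text or in Table 1. The Missing data and sample size sections add a second route to a first-period analysis, for the case that many patients are seen only once.

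**The concern.** Site is the only stratification factor. It may also carry differences in case mix and in how raters use the scale, since each centre scores its own patients. Balancing the sequences within site removes site from the true sampling error of a between-sequence comparison. An analysis without site leaves it in the estimated error. The standard error is then too large, the test is conservative and power is lost.

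This is more than silence in a condensed article, because the model terms are listed. Four parts of the plan compare patients with one another and are exposed:

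- the place-by-period test, which in an AB/BA design is a comparison of sequences and decides which analysis becomes the main one;
- the first-period-only analysis;
- the contribution of patients with one session to the mixed model;
- the rank pretest and its first-period fallback.

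**Working it through.** **The plan's own figure.** Inputs from the sample size section: "with a two-sided significance level of α = 5" per cent; an effect "similar to the standardised effect of 0.582 found for understanding in EmMa project"; an allowance to "compensate for power loss due to undetected differential carryover of up to 20% of the spatial intervention effect"; and "we will assume uncorrelated observations to be on the safe side". Differential carryover of 20% biases an AB/BA contrast by half that amount, so the effect is 0.9 × 0.582 = 0.5238 SD. The two-sample t-test then needs 78 per place for 90% power, and 80 gives 90.9%. This agrees with the article, which "results in a total sample size of 80 patients, 160 observations, for a power of 90" per cent.

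**Effect of site on that figure.** Write a patient's two scores as y1 and y2, each containing the same site shift s. In y1 − y2 the shift disappears. A simulation of the place contrast (80 patients, within-patient correlation 0.3, site gap 1 SD, no carryover) gave 99.1% power both with and without site.

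**First-period comparison.** Take 40 per sequence, two equal sites, sequences balanced within site and effect 0.582. The site gap s, in SD units, is an assumption. Two equal sites that differ by s add s²/4 to the pooled variance.

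*Reading A: the planning SD is the within-site SD (variance 1).* The unadjusted test estimates variance 1 + s²/4, while the true sampling variance corresponds to 1. With k = √(1 + s²/4), size = 2[1 − Φ(1.96k)]. Power follows from the noncentral t with noncentrality 0.582 × √20 = 2.603 and the critical value multiplied by k.

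| s | k | 1.96k | True size | Power without site | Power with site |
|---|---|---|---|---|---|
| 0 | 1.000 | 1.960 | 5.0% | 72.9% | 72.9% |
| 0.5 | 1.031 | 2.020 | 4.3% | 70.9% | 72.9% |
| 1.0 | 1.118 | 2.191 | 2.8% | 64.7% | 72.9% |

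Simulation with 40,000 runs agrees to within half a percentage point.

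*Reading B: the planning SD already contains the site variation (total variance 1).* The residual variance after adjustment is 1 − s²/4. Planned power without site is 72.9% at any gap. With site it is 75.6% at 0.5 SD and 84.3% at 1.0 SD. The unadjusted test's actual power, simulated with 20,000 runs, is about 73.5% and 75.3%, so the real gain is about 2 and 9 points.

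**Carryover test.** Simulated under reading B with 80 patients and carryover as large as the place effect:

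| Correlation | s | Size without site | Power without site | Power with site |
|---|---|---|---|---|
| 0.3 | 0.5 | 4.0% | 35.0% | 38.7% |
| 0.3 | 1.0 | 1.2% | 31.3% | 52.6% |
| 0.5 | 0.5 | 4.1% | 30.6% | 34.0% |
| 0.5 | 1.0 | 1.6% | 27.6% | 44.2% |

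With site in the model the size is about 5% in each row.

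**Rank test, first period** (4,000 runs, reading B). Pooled Wilcoxon against van Elteren: 70.7% against 72.9% at 0.5 SD, and 72.7% against 81.8% at 1.0 SD.

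**A caution on the baseline.** The article gives 58% power for 80 first measurements. That does not reproduce at 0.582 (72.9%) or at 0.5238 (63.8%). The 80% it gives after adding 16 patients (96 in all) does reproduce at 0.582 (80.6%), so 0.582 is used here. The mismatch is a separate matter and does not alter the comparison with and without site.

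**The case against.** The strongest objection is that the planned estimand is the place contrast from both periods, which a constant site difference cannot touch. The exposed steps are a pretest for carryover that the article does not expect, a fallback analysis and exploratory rank tests. The loss needs a site gap that the article does not give. It is nil at zero and about 2 points at 0.5 SD in the first-period comparison. Both clinics use the same eligibility criteria and a standardised instrument, and the error is conservative. All of this stands and limits the weight of the point. It does not remove it: the carryover test decides which analysis is the main one, and the listed model leaves out the one factor used to stratify.

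A reader might infer more, in four ways that the article does not support:

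- **The trial is underpowered or type I error is inflated.** Neither follows: the 90% is unchanged and size falls below 5%.
- **A site-specific period shift also enlarges the error of the within-patient contrast.** Nothing in the article suggests such a shift.
- **An effect produced by one site's unblinded raters could not be seen.** Site is known for every patient, so the place effect can be summarised by site without a model term.
- **A place-by-site term would settle the question of rater bias.** It cannot detect bias shared by both sites. With 40 per site and uncorrelated scores, its standard error is √(2/40 + 2/40) = 0.32 SD. A full 0.582 effect at one site and none at the other would be detected with a probability of only about 45%.

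**Conclusion.** The point holds as a low-cost improvement to a stated model. It does not invalidate the primary analysis. Omitting site leaves the complete-pair place contrast and its planned power intact. It makes the between-patient steps conservative, by an amount that depends on an assumed site gap. In the first-period comparison adjustment is worth nothing at no gap, about 2 points of power at 0.5 SD, and about 8 to 9 points at 1.0 SD, the last depending on whether the planning SD already contains site variation. In the carryover test it is worth about 3 to 4 points at 0.5 SD and 17 to 21 points at 1.0 SD, for carryover as large as the place effect and correlations of 0.3 to 0.5. These figures assume equal site sizes, balanced sequences within site and normally distributed scores.

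**What to change.** Add site as a fixed effect to the mixed models, including the place-by-period test, and to the first-period-only analysis. Replace the pooled Wilcoxon-Mann-Whitney tests with the site-stratified van Elteren version, in both the pretest and the main test. State this before the data are analysed. A summary of the place effect by site may be added as description, with a note that it is imprecise at 40 per site and says nothing about rater bias common to both. The cost is one degree of freedom, with no change to data collection, randomisation or sample size.

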**Fig. 2 Fig2:**
[figure not shown]
Scenarios considered in the simulation. Scenario A is the basic scenario with only a location, but no carryover or period effects. Scenarios B and C include a carryover and a period effect amounting to 20% of the location effect respectively, and in scenario D, both are included. The standard deviation of the score is 2.83 in all scenarios

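### The carryover pretest that decides between both-period and first-period data raises the primary test's type I error above the stated 5%, to about 6.4% to 6.8% at the protocol's own correlations

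*Protocol article*

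**What the plan says.** Under Statistical analysis, the primary endpoint (the CAT-AD reasoning subscore) is analysed with a linear mixed model containing place, period and their interaction, with patient as a random effect. The interaction test serves as the carryover check and decides what follows:

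- Not significant: "If there is no significant interaction effect, differential carryover can be neglected".
- Significant: "Otherwise, statistical analysis will be stratified by period, whereby the main analysis will be restricted to the first period", and second-period data move to a sensitivity analysis.

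The secondary endpoints examined with Wilcoxon-Mann-Whitney tests follow the same switch: "If the pretest is significant, the main test will only be performed on data from the first period".

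Under Calculation of sample size, the trial is sized "with a two-sided significance level of α = 5"%, giving a "total sample size of 80 patients, 160 observations, for a power of 90"%. The same section confirms that the primary endpoint is evaluated in two steps and reports a simulation of that procedure. It names the place contrast from both periods as the relevant quantity. It also concedes that a crossover trial powered for the place effect is unlikely to detect differential carryover, and that "slight differential carryover will still bias the effect". The Fig. 2 caption lists four simulation scenarios, beginning with: "Scenario A is the basic scenario with only a location, but no carryover or period effects". No separate level for the pretest and no adjustment of the 5% are given.

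**The concern.** This is the classical two-stage rule for an AB/BA crossover. The interaction is tested on each patient's sum over the two periods, and that sum contains the first-period score. If the sequence groups happen to differ by chance, the pretest tends to be significant, and so does the first-period comparison that is then run at the full 5%. The two steps together therefore reject a true null more often than 5%.

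The level of the single primary test is at stake, and so is the meaning of a first-period estimate that would be reported only because an imbalance had been seen. A check on carryover could justify some cost if it caught carryover of the size the protocol has in mind, so its power against the planned 20% also has to be worked out.

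**Working it through.** **Inputs from the protocol article.** Two-sided 5%; 80 patients, taken as 40 per sequence (two orders, blocks of 4); standardised effect 0.582; carryover allowance up to 20% of the effect; within-patient correlation ρ of 0 (planning) and 0.2 (example).

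**Assumptions.** Pretest level 5%, with 10% as a variant; ρ of 0.5 and 0.8 to show the range; equal variances in the two periods; scores in SD units.

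**1. The plan's own sample size.** Carryover of 20% biases the both-period contrast by half of that, so the effective effect is 0.9 × 0.582 = 0.5238. A two-sample t-test calculation at ρ = 0 gives 77.6 observations per place for 90% power (stated 80, where power is 90.9%) and 58.2 for 80% (stated 60, where power is 81.2%). With ρ = 0.2 and 48 patients, power is 81.0% (stated 80%). The stated figures are reproduced.

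**2. Type I error of the two-step rule.** Let C be the pretest statistic (patient sums compared between sequences) and T1 the first-period statistic. Cov(Y1+Y2, Y1) = 1+ρ and Var(Y1+Y2) = 2(1+ρ), so under the null corr(C, T1) = √((1+ρ)/2). Within-patient differences are independent of sums, so the both-period test keeps its 5% when the pretest is not significant. Hence

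type I error = 0.95 × 0.05 + 0.05 × P(T1 significant | C significant).

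| ρ | corr(C, T1) | P(T1 sig. given C sig.) | Type I error |
|---|---|---|---|
| 0 | 0.707 | 0.338 | 0.0475 + 0.0169 = 6.4% |
| 0.2 | 0.775 | 0.408 | 0.0475 + 0.0204 = 6.8% |
| 0.5 (assumed) | 0.866 | 0.533 | 0.0475 + 0.0267 = 7.4% |
| 0.8 (assumed) | 0.949 | 0.705 | 0.0475 + 0.0353 = 8.3% |

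Simulation with 40 per sequence agrees. In the order of the table, t-tests give 6.4%, 6.8%, 7.3% and 8.3%, and a mixed model gives 6.8%, 6.9%, 7.4% and 8.2%. Always using both periods gives 4.9% to 5.1%, except 5.5% for the mixed model at ρ = 0, where the patient variance sits on its boundary. With a 10% pretest the two-step rule gives 7.0% (ρ = 0) to 9.1% (ρ = 0.8).

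**3. What the pretest can detect.** Carryover of 20% is 0.2 × 0.582 = 0.1164 SD. The standard error of the sum contrast is √(2(1+ρ) × 2/40), which is 0.316 at ρ = 0. The non-centrality is 0.1164/0.316 = 0.368, and the power is Φ(0.368 − 1.96) + Φ(−0.368 − 1.96) = 0.056 + 0.010 = 6.6%. At ρ = 0.2 it is 6.3%. The false-alarm rate is 5%.

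**4. The first-period estimate after a significant pretest.** Its mean error is corr(C, T1) × √(2/40) × E[Z | pretest significant], where Z is the standardised error of C. Without carryover the last factor is 0 by symmetry, so there is no mean bias, but the estimate is over-dispersed: in simulation at ρ = 0 its SD is about 0.40, against 0.22 without selection. With 20% carryover in the direction that shrinks the both-period contrast, the factor is 1.31 at ρ = 0, and 0.707 × 0.2236 × 1.31 = 0.21 SD. At ρ = 0.2 the figure is also about 0.21 SD. Against a planned effect of 0.582, that is roughly a third.

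**5. Power with and without the pretest** (ρ = 0, 80 patients, t-tests). Without carryover: 93.3% two-step, 95.3% always both periods. With 20% carryover: about 90.2% and 90.5%.

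**The case against.** The strongest reply is that the excess is modest and several harsher readings go too far. Much of this stands.

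- A reader might take about 8% as the true level. The article uses only correlations of 0 and 0.2, so its own assumptions support an excess of 1.4 to 1.8 percentage points. Higher figures rest on assumed correlations, or on an assumed 10% pretest.
- A reader might say that the secondary analyses also break their level. The 5% appears only in the sample size calculation for the primary endpoint, and the secondary analyses are described as exploratory. No level is promised for them.
- A reader might call the two remarks on carryover a flat contradiction. Read together, they accept undetected carryover of up to 20% and enlarge the sample for the power it costs. The statement that it can be neglected is loosely worded, but this is a tension and not a formal contradiction.
- A reader might infer that the first-period estimate is always biased after a significant pretest. Without carryover it is not biased on average.
- A reader might suspect that the reported place term would be a first-period contrast because of how the interaction is coded. The article states no coding, and it names the both-period contrast as its target.
- The simulation was presented as a sample size check, for which scenarios with an effect are appropriate. The article supports only the statement that none of the four scenarios described is a null scenario.
- The power loss is small, and every scenario stays at or above the planned 90%.

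None of this restores the 5% level. The switch is a written decision rule for the primary endpoint, and the inflation is present at every correlation from 0 upward, with no carryover at all.

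**Conclusion.** The concern holds for the primary endpoint. As written, the two-step rule has a type I error of about 6.4% to 6.8% at the article's own correlations, and about 7.4% and 8.2% at assumed correlations of 0.5 and 0.8. These figures assume 80 patients, a 5% pretest, and neither a place effect nor carryover. Once the fallback is triggered, it rejects a true null in about a third of trials at ρ = 0, and in more at higher correlations.

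The pretest offers almost no protection in exchange, with about 6% power against the carryover the trial is planned to tolerate. If that carryover is present and dilutes the contrast, a first-period estimate reported after a significant pretest is on average about 0.2 SD too large. The simulation scenarios described all contain a place effect, so they do not show that the level is controlled.

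**What to change.** In Statistical analysis, remove the interaction test as a decision rule for the primary endpoint. Base the primary inference in every case on the both-period within-patient place contrast, from a mixed model with place and period as fixed effects and patient as a random effect. Report the place-by-period estimate with its confidence interval descriptively, and give the first-period contrast as a labelled sensitivity analysis. Use the same approach for the exploratory secondary analyses, including the rank tests (within-patient differences compared between sequences), for consistency.

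This changes one paragraph and needs no extra patients: 80 still give about 95% power without carryover and about 90.5% with 20%, at ρ = 0. The real cost is that differential carryover remains in the estimate, with a bias of half the carryover, so up to 10% of the effect at 20%. The sample size covers the resulting loss of power but not the bias, and nothing guarantees that carryover stops at 20%. The change therefore relies on the protocol's own expectation of no substantial carryover, and the write-up should say so.
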